#### 2.6.2. EA group

Subjects will receive EA treatment in the same manner as in the EAWN group. All treatment procedures for EA will be exactly the same as those used in the EAWN group, except that no warm needling therapy will be provided.

#### 2.6.3. Waitlist control group

No intervention will be provided for the waitlist control group, and the subjects in this group will be followed up during the 10-week observation period following the baseline assessment. In addition, the participants in this group will be assessed at weeks 5 and 10. After the 10-week waiting period, the participants in the control group will be re-randomized to receive free EAWN or EA treatments for tinnitus using the same treatment protocol that was administered to those in the EAWN or EA group. This is in consideration of the ethical implications of withholding potentially beneficial treatment during the 10-week waiting period.

### 2.7. Concomitant care and intervention

During the entire study period, each subject will be informed to avoid receiving other forms of intervention for tinnitus as they could influence the study results, including but not limited to other acupuncture treatments, behavioral therapy, and medication. Furthermore, the subjects will be advised by the practitioner to avoid other treatments, which will be reinforced by the investigators during the entry period and at each treatment session or evaluation time point. If a subject has attended other co-interventions for tinnitus, it should be reported to the investigators during each evaluation time, and the information will be recorded for analysis.

However, for basic diseases such as hypertension, diabetes, hyperlipidemia, coronary heart disease, and other complicated chronic diseases, subjects must continue taking their routine medication and other therapies. The research staff will record the names of the diseases, medications, and therapies in the case report form. This study will not provide posttrial care.

### 2.8. Study termination rules

The study may be terminated under the following circumstances: Participants experience serious adverse reactions or other complications that the investigators decide it is not safe to continue the study; Participants could not benefit or even get worse from the study treatment that the investigators consider necessary to terminate the study treatment; Participants who, for whatever reason, are unwilling or unable to continue the study and request the investigators to withdraw and discontinue the trial.

### 2.9. Outcome measurements

In this study, the unit of analysis is on an individual basis. Subjects with unilateral or bilateral tinnitus will be included without discrimination. Outcomes for tinnitus will be assessed at the side with more severe symptoms. Assessments and questionnaires will be administered at baseline (before intervention), week 5 (posttreatment), and week 10 (5-week follow-up).

#### 2.9.1. Primary outcome

Tinnitus loudness is a main symptom of tinnitus. The primary endpoint of our study will be the change in NRS score for tinnitus loudness from baseline to treatment completion (week 5). Changes in the mean NRS score for tinnitus from baseline to week 10 (5 weeks after treatment completion) will also be assessed. The NRS for the loudness of tinnitus is a widely used measurement for tinnitus.^[2]^ Subjects will rate the loudness of tinnitus using an 11-point NRS (0 − 10) with 0 indicating “no tinnitus”, and 10 indicating “maximum intolerable tinnitus”. The higher the score, the greater the tinnitus loudness and its effect.

#### 2.9.2. Secondary outcome

Tinnitus handicap inventory (THI) will be used as the secondary outcome measurement. The THI is a commonly used self-report measure for evaluating the extent of tinnitus-related distress with good reliability and validity.^[30]^ In this study, the validated Chinese (Cantonese) version of the THI will be adopted.^[31]^ This questionnaire consists of 25 items and can be categorized into 3 subscales: functional (12 items), emotional (8 items), and catastrophic (5 items). Each item will be scored on a 3-point rating scale. A yes will score 4 points; sometimes, 2 points; and no, zero points. The total THI score range from 0 to 100, with a higher score indicating a greater impact of tinnitus on the patients quality of life.

### 2.10. Safety assessment

Subjects will be asked to report any adverse events. Adverse events related to acupuncture and moxibustion include pain, bruising, bleeding, burns, blisters, dizziness, anxiety, and infections.^[32,33]^ For safety concerns and evaluations, all unexpected and unintended responses that are not necessarily related to the study treatment will be recorded with a detailed explanation including time of occurrence, duration of symptoms, seriousness (mild, moderate, or severe),^[32]^ management measures, time of adverse reaction disappearance, and causality categorization (certain, probable or likely, possible, unlikely, unclassified, or unclassifiable)^[34]^ at every visit on an adverse event form. Site investigators will record and deal with all adverse events regardless of whether they are relevant to the study treatment.

### 2.11. Dropouts and withdrawals

The participants are able to withdraw from the study for any reason at any time. All dropouts and attritions during the course of the study will be monitored and recorded with respective reasons.

### 2.12. Data collection and management

All participants’ data will be collected after obtaining signed consent forms. The participant’s privacy will be strictly protected throughout the trial. Investigators are responsible for maintaining the anonymity of the subjects. Participants will be assigned code numbers as identifiers and their confidentiality will be protected by the study identification number. The collected data will be anonymized and recorded on case report forms. All paper-based data will be checked and input into a password-protected electronic database. Two data entry persons will enter all data into an electronic database by double data entry to ensure data accuracy. All data will be kept confidential and access to the data will be limited to delegated research personnel. The participants study information will not be released outside the study without obtaining written permission from the participant. After the trial, all documents will be preserved in secured research archives for 7 years and will be deleted after the completion of the storage period.

### 2.13. Statistical analysis

#### 2.13.1. Sample size calculation

The sample size calculation will be based on the primary outcome measure of the NRS score of the loudness of tinnitus (0 − 10 points) and performed using OpenEpi.^[35]^ An estimation of the between-group difference and standard deviation is necessary because of the lack of similar comparable studies. In this study, we assume that similar differences in the NRS score of tinnitus loudness will be detected between the EA and waitlist control groups or the EAWN and waitlist control groups. We presume that a clinically significant difference of mean 2-point reduction and standard deviation of 2.49 in the NRS score of tinnitus loudness is detected based on previous studies^[36,37]^ and expert opinion. Using a 2-sided test, an alpha value of 0.05, and a power of 80%, it is estimated that 25 subjects will be required per study group. Considering a 20% attrition rate, the sample size for each group will be 30 subjects, which implies a total sample size of 90 subjects for the entire trial.

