## 2. Methods

### 2.1. Study design and setting

This study is a prospective, multicenter, assessor-blind, triple-arm, parallel-group, randomized controlled trial with a 1:1:1 ratio of group allocation to EA, EAWN, or waitlist control (control group, who can receive acupuncture treatment after a 10-week waiting period). Ninety eligible participants will be recruited for this study. The entire study period will last for 10 weeks, including a 5-week intervention period and a 5-week follow-up period. Outcome assessments will be performed at baseline and at weeks 5 and 10 through telephone or face-to-face evaluations. The study will be conducted at 3 Chinese medicine clinics under the management of Pok Oi Hospital, namely, Pok Oi Hospital − The Chinese University of Hong Kong Chinese Medicine Clinic cum Training and Research Centre (Shatin District), Pok Oi Hospital − The Chinese University of Hong Kong Chinese Medicine Clinic cum Training and Research Centre (Yuen Long District), and Pok Oi Hospital − Chinese Medicine Polyclinic (Tin Shui Wai). The study protocol is written following the Standard Protocol Items: Recommendations for Interventional Trials 2013 Statement and the Standard Protocol Items for Clinical Trials with TCM 2018 checklists.^[15,16]^

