#### 2.13.2. Statistical method and analysis

Statistical analysis of the collected data will be performed using IBM SPSS Statistics 27 (IBM Corp, Armonk, USA). An intention-to-treat approach will be used in this study. All randomized subjects will be included in the analysis, regardless of whether they received treatment. In addition, interim analyses will not be performed.

Descriptive statistics will be used to summarize participants baseline characteristics by group using mean (standard deviation), median (interquartile range), or number (percentage) as appropriate. All measurement data will first be assessed using normality tests. One-way analysis of variance or Welch analysis of variance will be used for comparison among the 3 groups for continuous variables. Categorical variables will be compared using the Pearson chi-squared test (or Fisher exact test).

Analyses of the primary and secondary continuous outcome variables among the 3 study groups (EA, EAWN, and waitlist control) overtime (baseline, weeks 5 and 10) will be performed using linear mixed models for repeated measures analysis, with treatment, time point, and interaction between treatment and time point included as fixed effects, within-person correlation modeled as a random effect, and age and tinnitus duration adjusted as covariates in the model. Missing data will be processed using the mixed effects model, assuming missing at random. Significant results (significant interaction, time × study groups) will be subject to post hoc tests to determine which group scores differently. Mean differences at weeks 5 and 10 will be estimated by the treatment × time interaction term, with associated 95% confidence intervals and *P* values.

Comparisons between the EA and EAWN groups for the adverse event rate among the 3 groups will be evaluated using the Pearson chi-squared test (or Fisher exact test).

The results will be considered statistically significant at a probability level of *P* < .05 with a 2-sided test throughout the analysis. In post hoc tests, we will employ the Bonferroni correction method and appropriately adjust the overall level of significance for multiple primary and secondary outcomes at different time points.

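### The 80% power is computed at an uncorrected 0.05, but the planned group comparisons are Bonferroni-corrected, so power per contrast is lower than stated

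*Protocol article*

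**What the plan says.** Section 2.13.1 assumes that a similar difference "will be detected between the EA and waitlist control groups or the EAWN and waitlist control groups". The inputs are a "clinically significant difference of mean 2-point reduction and standard deviation of 2.49 in the NRS score of tinnitus loudness". The result is: "Using a 2-sided test, an alpha value of 0.05, and a power of 80%, it is estimated that 25 subjects will be required" per group. The allowance for loss follows: "Considering a 20% attrition rate, the sample size for each group will be 30 subjects", 90 in all. No multiplicity adjustment enters this calculation.

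Section 2.9.1 names one primary endpoint, the change in NRS loudness from baseline to week 5. Week 10 is assessed as well, and the THI is the secondary outcome (section 2.9.2).

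Section 2.13.2 fits a linear mixed model to the three groups over time. If the time-by-group interaction is significant, post hoc tests show which groups differ. A two-sided 0.05 is the general level ("The results will be considered statistically significant at a probability level of" that size). For the post hoc tests, "we will employ the Bonferroni correction method and appropriately adjust the overall level of significance for multiple primary and secondary outcomes" at the different time points. The number of tests in this correction is not stated.

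**The concern.** The sizing level and the testing level do not match. Section 2.13.1 gives each of two contrasts the full 0.05. Section 2.13.2 makes the same contrasts share 0.05 with at least one other test. If all three pairs are tested, EA versus EAWN also takes a share, although the sizing does not cover it. The sentence on several outcomes and time points could enlarge the family further, although there is only one primary endpoint at one time.

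Two things are at stake. First, the chance of missing a true 2-point benefit of a given regimen is larger than the 20% that the protocol implies. Second, with the family left open, readers cannot tell which threshold the primary contrasts must meet.

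**Working it through.** **Inputs, all from section 2.13.1 unless noted.** Difference 2; SD 2.49; two-sided 0.05; power 80%; 25 evaluable per group; 30 randomised per group; 20% attrition, so 30 × 0.8 = 24 completers. Allocation is equal (section 2.1: "1:1:1 ratio of group allocation to EA, EAWN, or waitlist control"). The number of tests k is an assumption: k = 2 for the two sized contrasts, k = 3 for all pairs at one time point.

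**Step 1: the plan's own figure.** n = 2 × [(1.960 + 0.842) × 2.49 / 2]² = 24.3, rounded up to 25. The stated figure reproduces at an uncorrected 0.05. At n = 25, power is 81.1% by the normal approximation and 79.5% by the t test.

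**Step 2: power per contrast at the corrected level.** Two-sample t test, level 0.05/k, df = 2n − 2, noncentrality = 2 / (2.49 × √(2/n)). For n = 25 the noncentrality is 2.84. The critical value is 2.01 at 0.05, 2.31 at 0.025 and 2.48 at 0.0167.

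| Evaluable per arm | k = 1 (0.05) | k = 2 (0.025) | k = 3 (0.0167) |
|---|---|---|---|
| 24 | 77.8% | 67.9% | 61.9% |
| 25 | 79.5% | 70.0% | 64.1% |
| 30 | 86.4% | 78.9% | 73.9% |

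The normal approximation at n = 25 gives 72.5% (k = 2) and 67.2% (k = 3).

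**Step 3: a wider family.** As an illustration only, three pairs at two time points (k = 6, level 0.0083) give 53.9% at n = 25.

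**Step 4: evaluable patients needed for 80% per contrast (t test).** 31 per arm for k = 2 and 34 for k = 3. Dividing by 0.8 for attrition gives 39 and 43 randomised per arm, against 30 planned.

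**Step 5: the two contrasts jointly.** They share the waitlist arm. In a simulation with both true effects equal to 2 and 25 per arm, Bonferroni gives:
- at least one active arm superior: about 85% (k = 2) or 80% (k = 3);
- both superior: about 56% or 49%.

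Holm over the two contrasts gives about 76% per contrast and 67% for both with 25 per arm, and about 74% and 64% with 24. These joint figures move by a point or so with the variance estimate: pairwise t tests give 84.3% for at least one arm at k = 2, and a pooled three-arm variance gives 84.7%.

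**Step 6: the interaction gate.** With an overall three-group test at one time point as a stand-in, power per contrast at k = 3 (normal approximation, n = 25) is 67.1% with the gate and 67.2% without. The gate neither explains nor repairs the gap.

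**The case against.** The strongest reply is that the trial as a whole is not underpowered. The sizing sentence joins the two contrasts with an *or*, and the protocol never says that both must succeed. If one successful arm is enough, power stays at about 85% or 80%. That stands: a reader might infer that the trial has only 64 to 70% power, and the documents do not support that. Those figures are per contrast, for two or three tests and 25 evaluable per arm. The reply does not rescue the stated 80%, though. It was computed for one contrast, and the stated aim is to assess both regimens.

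A second reply is that 24 or 25 evaluable is pessimistic. All randomised subjects enter a mixed model that assumes data missing at random, and the 20% attrition is not tied to week 5. This also stands, which is why the range runs to 30 per arm. Even there the t test gives 78.9% and 73.9%. The model might recover some power if 2.49 is the SD of raw scores, but the protocol does not say so and gives no correlation.

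Third, a reader might infer that the threshold could be anything from 0.05 down to 0.05/12, about 0.004. The text does not support either end firmly. The 0.05 is a general level, and the next sentence sets an exception for post hoc tests, so the two do not contradict each other. No section defines a twelve-test family. A condensed article may also leave the exact family to a fuller document. But no family of two or more tests restores 80% per contrast with the stated inputs and 25 per arm.

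Finally, a pairwise correction that includes EA versus EAWN is defensible, because the Introduction lists comparison of the three groups as an aim. The fault lies in the power statement, not in the wish to correct.

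**Conclusion.** The concern holds as a mismatch between a stated power and the tests it is meant to describe. The 25 per group is not an arithmetic error; it belongs to an uncorrected 0.05, which is not the level of the planned post hoc comparisons. Per-contrast power is 67.9% to 78.9% for two tests and 61.9% to 73.9% for three, for 24 to 30 evaluable per arm. It is lower still if the correction spreads over outcomes and time points.

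These figures rest on the protocol's difference and SD, a two-sample t test, and an assumed number of tests. The effect is a higher risk of a false negative for each regimen. It does not bias the estimates or inflate the type I error. It should be fixed, but it does not undermine the trial.

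**What to change.** In section 2.13.2, define the confirmatory family for the single primary endpoint (week-5 NRS change) as the two contrasts that were sized: EA versus waitlist and EAWN versus waitlist. State that this correction is not spread over week 10 or the THI. EA versus EAWN may stay as a separate supportive comparison with a 95% confidence interval.

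In section 2.13.1, restate power at the level actually used:
- Bonferroni at 0.025: about 70% per contrast with 25 evaluable per arm, 68% with 24.
- Holm over the two contrasts, both effects equal to 2: about 76% per contrast with 25 (74% with 24), and about 67% (64%) for both.
- All three pairs kept in the family: about 64% per contrast with 25, 62% with 24.

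State also whether success means at least one active arm or both, since the power differs widely between the two.

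The cost is wording in two sections, a less favourable stated power, and the loss of confirmatory status for EA versus EAWN. No extra patients are needed.

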## Abstract

**Methods::**

This study is a prospective, multicenter, assessor-blind, 3-arm, parallel-group, randomized, waitlist-controlled trial. In total, 90 patients will be randomly assigned to the electroacupuncture, electroacupuncture and warm needing, or waitlist control group in a 1:1:1 ratio. Patients in the 2 treatment groups will be treated twice a week for a total of 5 weeks. Patients in the control group will not receive treatment during the study period and will be informed that they can receive it for free after a 10-week waiting period. The duration of intervention for this study will be 5 weeks, followed by another 5 weeks for the posttreatment assessment. The primary outcome is the change in the visual analog scale score for tinnitus loudness from baseline until the end of treatment. The secondary outcome is the tinnitus discomfort assessment measured using the Tinnitus Handicap Inventory. Outcome parameters will be assessed at baseline and at weeks 5 and 10. Any adverse events will be observed and recorded for safety assessment. Linear mixed models for repeated measures will be applied in the analysis.

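### Thirty per group less 20% attrition leaves 24, one short of the 25 per group that the protocol says it requires

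*Protocol article*

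**What the plan says.** Section 2.13.1 sizes the trial on the NRS for tinnitus loudness. The contrast is each acupuncture arm against waitlist, with the same difference assumed "between the EA and waitlist control groups or the EAWN and waitlist control groups". The inputs are "a clinically significant difference of mean 2-point reduction and standard deviation of 2.49 in the NRS score of tinnitus loudness", a two-sided alpha of 0.05 and 80% power. From these the section concludes that "it is estimated that 25 subjects will be required per study group".

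The next sentence adds the allowance for loss: "Considering a 20% attrition rate, the sample size for each group will be 30 subjects, which implies a total sample size of 90 subjects". The abstract repeats the total: "In total, 90 patients will be randomly assigned". The article does not give the formula that turns 25 into 30, and no other section gives a different attrition rate or a different required number.

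**The concern.** An attrition rate ordinarily means the share of randomised patients who are lost. The number to randomise is then the required number divided by the share retained, not the required number multiplied by one plus the rate. The two differ: 20% of 30 is 6, whereas the allowance built into 30 is only 5 above the required 25.

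The article therefore prints three figures (25 required, 20% loss, 30 randomised) that do not agree. Anyone following retention against the plan would take six losses per group as covered when only five are. The stated power also rests on a number of evaluable patients that the plan's own attrition rate does not deliver.

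**Working it through.** **Inputs, all from section 2.13.1:** difference 2 points; SD 2.49; two-sided alpha 0.05; power 80%; required 25 per group; attrition 20%; 30 per group, 90 in total.

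**Step 1. Reproduce the 25.** With the normal approximation for two means,

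n = 2 × [SD × (z for alpha/2 + z for power) / difference]² = 2 × [2.49 × (1.960 + 0.842) / 2]² = 24.33, rounded up to 25.

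This matches the article. The t-test calculation gives 25.33, rounded up to 26, so the stated 25 is a normal-approximation figure.

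**Step 2. Try to reproduce the 30.**

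| Route | Result |
|---|---|
| 25 × (1 + 0.20) | 30 exactly |
| 25 / (1 − 0.20) | 31.25, rounded up to 32 |
| 24.33 / (1 − 0.20), base not rounded first | 30.4, rounded up to 31 |

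The stated 30 is consistent with the first route. Rounding up after dividing by the share retained does not give 30, even from the unrounded base.

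**Step 3. Apply the stated loss to the stated number.** 30 × (1 − 0.20) = 24. This is below 25 and also just below the unrounded 24.33. It holds however the 30 was reached.

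**Step 4. Find the loss that 30 can absorb.** 1 − 25/30 = 16.7%, or 5 of 30.

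**Step 5. Find the number that 20% would need.** 32 per group, 3 × 32 = 96 in total, 6 more than planned. Check: 32 × 0.80 = 25.6, at least 25.

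**Step 6. Power for one arm against waitlist, two-sided alpha 0.05.** By the normal approximation, power = Φ[2 / (2.49 × √(2/n)) − 1.960].

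| Evaluable per group | Normal approximation | t-test |
|---|---|---|
| 24 | Φ(2.782 − 1.960) = 79.5% | 77.8% |
| 25 | Φ(2.840 − 1.960) = 81.1% | 79.5% |

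The missing subject costs about 1.6 to 1.7 percentage points by either method.

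**The case against.** The strongest reply is that this hardly matters. By the method that yields the article's 25, power at 24 per group is 79.5%, half a point under the target, and 24 falls short of the unrounded need by a third of a subject. That stands, and it fixes the size of the point.

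A second reply concerns when patients are lost and how they are analysed. The article does not say by when the 20% is expected. The study runs for 10 weeks but the primary endpoint is at week 5. If part of the loss comes later, more than 24 per group have a week 5 value; 25 do if loss by week 5 is at most 16.7%. Assessment by telephone is allowed (section 2.1), so stopping treatment need not mean a missing score. Section 2.13.2 analyses all randomised subjects in a mixed model under missing at random. These points soften the shortfall but do not remove it. A patient lost before week 5 contributes only a baseline value and adds little to the primary contrast, and the sample size section itself treats attrition as a loss that must be made up.

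Three stronger readings are tempting, and the document does not support them:

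- **That the plan is known to have multiplied by 1.2.** No formula is given. It is the likeliest route, but 24.33/0.80 = 30.4 would also give 30 if rounded to the nearest whole number instead of up.
- **That power falls to about 78% because of the attrition step.** That is the t-test figure, and by the t-test the plan's own 25 also misses 80%, at 79.5%. Part of that gap comes from the choice of approximation.
- **That the shortfall should be added to a loss of power from the Bonferroni correction in section 2.13.2.** The sample size is set at alpha 0.05, and the article states no smaller alpha for it. Any effect of multiplicity is a separate question and should not lend weight to this one.

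**Conclusion.** The attrition statement is wrong as written, and the error is minor. Thirty per group does not preserve 25 evaluable per group at 20% attrition: it preserves 24, and it protects 25 only up to 16.7%. On the plan's own inputs, 20% attrition calls for 96 patients, not 90.

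The conclusion assumes that the attrition rate is a share of those randomised, that it falls equally on the groups, and, for the power figures, that it has occurred by week 5 and that lost patients carry no information on the primary contrast. The last two are the pessimistic end, so the true shortfall may be smaller. A reader might infer that the trial is materially underpowered or must recruit more; a change of about 1.6 points of power does not support that.

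**What to change.** Rewrite the attrition sentence in section 2.13.1 in one of two ways:

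1. State that 30 per group (90 in total) keeps 25 evaluable per group with up to 16.7% attrition.
2. Keep the 20% rate and state that it leaves 24 evaluable per group, with power of 79.5% by the normal approximation used for the 25 (77.8% by the t-test) at two-sided alpha 0.05.

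Either is enough. Enrolment, design and analysis stay as they are, and the total in the abstract stands. The cost is one sentence and a slightly less favourable stated attrition tolerance or power. Should the sponsor wish to hold both the 25 and the 20%, the matching figures are 32 per group and 96 in total, but the size of the shortfall does not demand it.
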